## Abstract

**Background:**

Childhood obesity is a concern in Australia and across the world. Community-based weight management programs are an important response to address childhood obesity. However, the scientific literature suggests that their effectiveness could potentially be enhanced by providing a structured incentive scheme. This proposal aims to determine the effectiveness of enhanced goal setting linked to a structured incentive scheme designed to improve the sustained health and wellbeing of overweight/obese children within the context of an existing community-based program.

**Methods/Design:**

This study is a cluster randomized controlled trial delivered within the context of the existing NSW “Go4Fun” program with a 10-week and 6- and 12-month follow-up (*n* = 40 sites, 570 participants) that compares the effectiveness of small changes to the program in which children were asked to set goals (supported by text messages) and were given rewards for achieving them (intervention). This will be compared to the standard/existing program (control), which did not have the same structured incentive program. Data will be collected for all participants at baseline, end of program, and at 6 and 12 months. The primary outcome is a mean change in body mass index (BMI) *z* score at the 12-month follow-up. Secondary outcomes include anthropometric measures (body weight, height, and waist circumference) and behavioral measures collected via validated questionnaires. A process evaluation (comprising surveys and focus groups) to determine acceptability and sustainability and to inform downstream translation will also be conducted.

**Discussion:**

This study will inform policy and program delivery as well as the broader evidence base regarding goal achievement and incentive schemes directed at children’s health-related behaviors and will provide evidence that is likely to be transferrable across a range of health conditions.

**Trial Registration:**

ACTRN12615000558527 registered on 29 May 2015.

## Background

### Childhood obesity problem definition

The prevalence of childhood overweight and obesity is increasing, contributes to a major public health problem, and has implications for current and future health services [1]. Results from the 2011/12 Australian Health Survey showed that one-quarter of all Australian children (around 600,000 children) aged 5 to 17 years were overweight or obese, up four percentage points from 1995 (21 %) [2]. The extent of the epidemic and its short- and long-term effects on the physical and psychological health (including a potential reduction in life expectancy for future generations) have made the prevention and treatment of childhood overweight and obesity a high priority [3]. Importantly, being obese or overweight as a child increases the risk of a range of noncommunicable (or chronic) diseases and disorders in adulthood such as type 2 diabetes and cardiovascular disease [4]. Obese children have a 50 % chance of being overweight or obese as adults, and adults who were overweight as children have higher risk of weight related ill health and early death than people who became obese in adulthood [1]. In addition, being overweight or obese as a child can impact self-esteem, willingness to participate in class/sporting activities, and socialization. Despite the high prevalence and existence of multiple national action strategies and guidelines, child-focused obesity services are limited and opportunities exist for optimizing health-related behaviors [5, 6].

### Targeted programs to address childhood obesity

Community-based weight management programs are an important response to address childhood overweight and obesity. International recommendations identify that the core elements of any initiative to address the widespread problem should involve the family and include nutrition education, promote physical activity and include strategies that target behavior modification [2, 7–9]. Two recent Australian randomized controlled trials (RCTs), namely PEACH (*n* = 169) [10] and HIKCUPS (*n* = 165) [11] highlight the importance of engaging and targeting parents in structured weight loss programs for overweight/obese children aged 5 to 9 years old. Another RCT (*n* = 111) found that a parent-directed approach based on parenting skills training with lifestyle education improved BMI z scores by approximately 10 % compared to approximately 5 % with parenting-skills training alone or wait-listing for intervention [12]. This study demonstrates the importance of including parents in strategies aimed at improving weight management in children. Although, the specific behaviors required for effective weight loss are well established, the challenges associated with the behavior change aspects of interventions are profound; therefore, for these and many other reasons, trials are often not upscaled and translated into a real-world context [9, 13, 14].

The United Kingdom Mind Exercise Nutrition Do it (UK MEND) program is an evidence-based community-based child weight management program with effectiveness in weight outcomes [15, 16]. The MEND RCT was designed to assess effectiveness of a 9-week intervention based on the principles of psychology, learning, and social cognitive theories. The MEND trial (n = 117) demonstrated that the intervention group had significantly reduced waist and BMI measures, as well as improvements in physical activity and self-esteem [16]. Based on these findings, and due to the growing burden of childhood obesity in New South Wales (NSW, Australia), MEND was translated into the NSW Health context in 2009. The program was named Go4Fun and places an emphasis on reaching disadvantaged communities and, accordingly, low socioeconomic and regional areas [17]. It is a community-based, multidisciplinary family-focused program that targets weight-related behaviors and self-esteem of children aged 7 to 13 years who are overweight or obese [18]. To participate, children must have a BMI > 85th percentile for their age and sex (as per the Australian Institute of Health and Welfare (AIHW) classification of overweight and obesity in children) [19]. The program is centrally managed by the NSW Office of Preventive Health, with NSW local health districts (LHDs) and the Better Health Company being responsible for delivery of the 10-week program. In line with current evidence about the importance of family engagement, both the parent/guardian and the child attend the weekly sessions.

While Go4Fun has demonstrated short- and medium-term health benefits for those who complete it, opportunities to improve retention and completion, goal setting and outcomes, and sustained outcomes after the program have been identified. A recent process evaluation found that despite the potential as a community-based population-wide program, widespread reach and attendance could be improved [17]. End of program results (10 weeks) are encouraging, with participating children achieving a mean reduction in BMI (0.7 kg/m^2^) and waist circumference (1.7 cm) as well as improvements in physical activity and self-esteem [18]. Some Go4Fun local program providers have tried to improve retention and goal achievement through the ad hoc use of incentives (such as stickers and loyalty cards and in some cases, vouchers), but these incentives are not standardized; nor have they been investigated in isolation. While a quality improvement framework is in place, great value exists in robustly evaluating whether or not a program can be improved by incentivization. This concept is supported by recent literature emphasizing the value of evaluation in policy and service improvement, where incremental changes supported by small scale and tightly focused approaches can lead to scalable impacts over time [20]. Therefore, research is needed to maximize the reach and value of Go4Fun and other weight management programs. One new approach is to consider behavioral and psychological literature relating to the use of incentives to support behavior change through goal setting.

### Behavioral insights literature

Challenges in facilitating behavior change, as it relates to human health, has led to increasing prominence of research investigating whether the use of incentive schemes (based on psychological and behavioral theory and research) might positively influence health-related behaviors [21]. As such, researchers have explored the potential value of incentives in the formation of exercise habits [22], weight loss [23, 24], and smoking cessation [25]. Two recent systematic reviews reporting studies in adults found interventions based on providing financial incentives are more effective than usual care for encouraging healthy behavior change [26] and that lucky draw style rewards were an effective mechanism for upscaling [26, 27]. The reviews also found that making rewards contingent on repeated behaviors maximised habit formation and sustainability [27]. Further research in adults has found that rewards for goal attainment (for example, the completion of daily walking) were more likely to have positive longer-term outcomes than simply rewarding outcomes (such as losing a certain number of kilograms) [28, 29]. Other studies have also demonstrated that treatments that focus on behaviors, rather than outcomes have been effective in numerous meta-analyses to change behavior in general [30] and for promoting physical activity [31]. In addition, evidence suggests that the use of small rewards can increase task perseverance as people are motivated to complete an action when they can see their progress [32].

Despite encouraging developments in adults, to date there has been very little research investigating the value of incentives for improving health-related behaviors in children. One French nonrandomized study (*n* = 1,589) investigated the effects of a school-based incentive program aimed at promoting physical activity [21]. Incentives were based on lottery style tickets earned by children when they participated in particular activities (for example, riding or walking to school) and they were entered into a regular prize draw ($10 sports store). The study found the incentive program increased the probability of physical activity and the authors conclude that the lucky draw aspect of the scheme provided a low-cost approach to promoting exercise in children [21]. Another RCT testing the effect of an incentive scheme aimed at improving fruit and vegetable intake by children found that at baseline 33 % of children ate at least one serving of fruit or vegetables during the school day and at follow-up this increased to an average of 60 % in the incentive group and remained unchanged (31 %) in the control group [33]. The authors also tested the difference between different reward schemes and found that immediate provision of rewards when goals were achieved resulted in a larger effect than delayed provision. Further insights can be gleaned from nonhealth related fields. A recent paper collates the findings of a series of school-based RCTs in more than 200 American urban schools testing the impact of financial incentives on student’s reading books and their reading achievement. This study found that incentives were more effective when they were given to children when they performed a behavior (in this case reading) rather than for achievement of an outcome (in this case exam results). Whilst this study has substantial limitations (for example, a lack of comparability across samples) it adds weight to the speculation on the impact of incentives in the achievement of behavioral goals (inputs) rather than health outcomes (outputs) in school-aged children [34].

The issue of sustainability of behavior, as it relates to incentives, is also an important area of consideration. Evidence suggests that incentivising activities and goals is more likely to have a long-term outcome than simply incentivising outcomes, which tends to have a powerful but often transient effect [32]. The theoretical concept is that incentives directed at activities and goals facilitates creation of behavioral habits that improve sustainability. However, there is very limited research that has tested retention of behavior change after incentives are ceased. Another area of research that has been shown to improve retention of health-related behaviors is the use of ongoing and regular text messages. These include RCTs demonstrating effectiveness of mobile phone text messaging to promote smoking cessation [35, 36], weight loss [37], physical activity [38], asthma medication adherence [39], and glycemic control in diabetes [40]. Further studies have examined the effects of text message reminders and support on medication adherence. The largest of these (538 participants) delivered text messages with health counsellor support over 12 months to HIV patients. Patients receiving the intervention had significantly improved adherence to antiretroviral treatment and rates of viral suppression compared with control individuals [41]. Other smaller studies have found improved self-efficacy and medication adherence for patients with diabetes [40] and asthma [39] and in pediatric transplant patients [42].

In summary, early research suggests that the use of incentives for promoting behavior change in overweight/obese children has potential, but to date, this is a relatively unexplored area. The overall objective of this research is to apply behavioral insights to determine the effectiveness of a structured goal setting and incentive scheme to improve health-related behaviors in overweight/obese children. The opportunity also exists to test, using text message reminders and lottery prize draw, whether any gains made during the program are maintained and whether the effects of incentives are sustained after the program, as a cost-effective way of engaging with families after the program. The specific aims of this research are as follows:To determine the effectiveness of a structured goal setting incentive scheme on the following:i.Health outcomes (body mass index (BMI) and waist *z* scores, BMI, waist circumference, nutrition, physical activity, and self-esteem) at the end of the program (10 weeks), 6 months, and 12 months;ii.Completion of at least 75 % of the Go4Fun weight management program and;iii.Achievement of physical activity and nutrition goals during the Go4Fun program.To determine the effectiveness of post program text message reminders highlighting a lottery prize draw on the following:i.Sustained health outcomes (BMI and waist *z* scores, BMI, waist circumference, nutrition, physical activity, and self-esteem) at 6 months, and 12 months after the program; andii.Achievement of physical activity and nutrition goals at the end of the program (10 weeks), 6 months, and 12 months after the program.To determine the acceptability (via a process evaluation) of the structured incentive scheme to inform widespread policy translation and implementation.

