### Randomization

Eligible sites have been randomized to either deliver the intervention (standard Go4Fun plus incentives) or control (standard Go4Fun) program for 10 weeks. Randomization was conducted using a computer-generated sequence (1:1) managed by the research team based at The George Institute and independent of the Department of Premier and Cabinet NSW (DPC), any program leader or LHD. Clusters were stratified according to local health district to ensure equal representation across groups within each LHD.

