### Intervention group

Sites randomly allocated to the intervention arm will deliver the Go4Fun program with the enhanced goal setting and structured incentive scheme developed during our preliminary work. As described above, the standard program consists of weekly group sessions (one per week) for 10 weeks during the school term. No sessions have been lengthened or combined for the intervention sites. All children participating in the intervention sites will receive the same information and participate in the same exercise and nutrition sessions as the control group. They will also receive the same system of “reward stickers” and standardized attendance rewards throughout the program. However, at intervention sites, participating children will be eligible to participate in an enhanced goal-setting component and receive incentives for reaching certain levels of goal attainment. That is, for the intervention, participants will set SMART [32] behavioral goals and achieving these goals will result in the incentives being provided. This emphasizes the importance of enhancing the goal-setting process, including resetting/stretching them if they are achieved too easily in the program, as well as linking goal achievement to incentives [32]. The incentives will only be received for the period of the 10-week program.

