The goal setting component and incentive scheme was developed and agreed upon during the preliminary work for this study with an overview of the goal setting enhancement and incentives being as follows:*Goal setting:* At the third session in the program, the children and their parent/ guardian in the intervention group are provided with an enhanced resource to guide them through jointly setting an exercise and a nutrition goal (child and parent/guardian in collaboration). Examples include ‘I will play soccer for 30 minutes on 3 days a week at the park with dad’ and ‘I will try a new vegetable two times a week for dinner on Wednesday and Sunday nights.’*Goal attainment incentives:* Children will receive milestone-based incentives for achieving their set goals. There will be three levels as follows: (i) a vegetable slicer once two exercise and two nutrition goals are achieved; (ii) a sports store voucher (value of $AUS10) once four exercise and four nutrition goals are achieved, and (iii) a height-adjustable tennis set once six exercise and six nutrition goals are achieved. In addition, Go4Fun leaders will ask the children on a weekly basis if they have achieved their goal and prompt them to reset them if they were too easy.*Goal attainment reminders via text message and lottery style incentive:* After the 10-week program, parents/ guardians will receive weekly mobile phone text message reminders to support and encourage children to achieve their goals (and set new ones where relevant). Parents/ guardians will be encouraged to text back with goal achievements with each goal achieved being rewarded with a ticket entry (maximum of eight tickets per month) into a prize draw (one per program) for a family pass to a local zoo (or similar family activity, depending on local availability) that will be drawn at 6 months.

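### Aim 2 asks for the separate effect of the post-program texts and lottery, but the two-arm design can estimate only the effect of the whole package at 6 and 12 months

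*Protocol article*

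**What the plan says.** The specific aims stand at the end of the section Behavioral insights literature. Two of them are worded as effectiveness questions about different things.

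- Aim 1: "To determine the effectiveness of a structured goal setting incentive scheme on the following". Its health outcomes are read at 10 weeks, 6 months and 12 months.
- Aim 2: "To determine the effectiveness of post program text message reminders highlighting a lottery prize draw on the following". Its health outcomes are the same ones, read at 6 and 12 months. Its second item is "Achievement of physical activity and nutrition goals at the end of the program (10 weeks), 6 months, and 12 months after the program".

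The section Randomization describes a single allocation: "Eligible sites have been randomized to either deliver the intervention (standard Go4Fun plus incentives) or control (standard Go4Fun) program for 10 weeks". The section Intervention group lists three elements under one scheme: goal setting, milestone incentives during the program, and a post-program element. Of the last it says: "After the 10-week program, parents/ guardians will receive weekly mobile phone text message reminders to support and encourage children". Goals reported by text earn tickets in a prize draw held at 6 months. The same section also says: "The incentives will only be received for the period of the 10-week program".

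The section Control group describes standard Go4Fun with attendance rewards and mentions neither texts nor a lottery. The section Statistical analysis plans one comparison, intervention against control.

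**The concern.** Aim 2 names the texts and lottery as the thing whose effect will be determined. To determine that effect, the trial would need sites that differ in the texts and lottery but not in the in-program scheme. None are described. The same 6- or 12-month difference could be reported once as an effect of the incentive scheme and once as an effect of the texts.

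This matters because the Discussion says the trial is to inform policy and program delivery. A reader deciding whether to fund the low-cost texting element alone could take a result under Aim 2 as direct evidence for it, although the trial holds no such evidence.

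**Working it through.** The point is structural, so it is checked by setting out what each arm receives and what the arm difference then contains. The plan states no figure for Aim 2 that could be reproduced.

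**What each arm receives**

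| | In-program goal setting and milestone incentives | Post-program texts and lottery |
|---|---|---|
| Intervention (20 sites) | yes | yes |
| Control (20 sites) | no | no |

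The 20 and 20 come from the section Sample size; the contents come from Intervention group and Control group. The cells "yes, no" and "no, yes" are empty. No second randomization is described.

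**What the arm difference contains.** At time t, let

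- A(t) be the effect of the in-program scheme, as it would stand without texts or lottery;
- B(t) be the effect of the texts and lottery;
- C(t) be any interaction between them.

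Then the expected arm difference is D(t) = A(t) + B(t) + C(t).

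- At 10 weeks no post-program text has been sent, so B = C = 0 and D(10 weeks) = A(10 weeks). This contrast isolates the in-program scheme.
- At 6 and 12 months there is one observed quantity, D(t), and at least two unknowns.

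**Illustration.** Take the planning difference of 0.24 in BMI z score from the section Sample size as D(12 months), and set C = 0 for simplicity.

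| A | B | D = A + B |
|---|---|---|
| 0.24 | 0.00 | 0.24 |
| 0.12 | 0.12 | 0.24 |
| 0.00 | 0.24 | 0.24 |

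The three rows imply the same expected arm difference. In the first the texts and lottery do nothing; in the last they do everything. More children or more sites would narrow the interval around D but would not tell the rows apart.

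**Can the 10-week result be subtracted?** D(12 months) − D(10 weeks) = [A(12 months) − A(10 weeks)] + B(12 months) + C(12 months). The bracket is the fading or persistence of the in-program effect without texts. No site shows it, so subtraction does not recover B.

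**The 10-week item in Aim 2(ii).** The texts begin after the 10-week program. Goal achievement at 10 weeks precedes them and cannot be an outcome of them.

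**The two statements on incentives.** One sentence in Intervention group confines incentives to the 10 weeks. The overview in the same section rewards goals achieved after the program with lottery tickets and heads that element as an incentive. Taken as written, the two do not agree.

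**The case against.** The strongest reply is that the protocol already has the right target elsewhere. Study design speaks of the effectiveness and sustainability of the enhanced intervention at 6 and 12 months. The text leading into the aims asks whether gains are maintained. Only one comparison is planned, and the question of which parts mattered most is given to the process evaluation. On this view Aim 2 is loose wording for a sustainability question.

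That is a fair account of what the design can do, and it shows that the correction is easy. It does not rescue Aim 2 as written, which asks for the effect of the texts and lottery. The process evaluation uses attendance and outcome data, surveys in the intervention group, leader interviews and focus groups; it adds no randomized contrast. An analysis plan could not supply one either.

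It can also be said that the sentence confining incentives to the 10 weeks refers to the milestone items only, and that the 10-week item in Aim 2(ii) is a starting level for judging maintenance. Both are possible. The text says neither.

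A reader might infer more than the document supports, in three ways.

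- *That Aim 1 is also not estimable at 6 and 12 months.* Aim 1 does not say the scheme acts alone, and Intervention group lists the texts and lottery within the goal-setting and incentive scheme. Aim 1 at those times can be read as the package contrast, which is estimable. Its 10-week and in-program items are unaffected.
- *That persistence after incentives end cannot be tested.* The only draw described is at 6 months and the primary outcome is at 12 months. Persistence of the package effect may be assessable there if texts and tickets stop with the draw, which is not stated. What cannot be assessed is persistence of the in-program scheme by itself.
- *That the primary result is compromised.* The 12-month arm difference validly estimates the package effect.

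**Conclusion.** The concern holds for Aim 2. The separate effect of the texts and lottery is completely confounded with the in-program scheme in all 40 sites, so the trial carries no randomized information on it at any sample size. Aims 1 and 2 share one contrast for the health outcomes at 6 and 12 months; only the 10-week contrast isolates the in-program scheme. The 10-week item in Aim 2(ii) and the two statements on when incentives are given are smaller faults of wording.

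This rests on three readings: that the texts start only after the program, as Intervention group says; that control sites receive neither texts nor lottery, as their description implies; and that the study schema, which is not shown, contains no further arm or re-randomization. Nothing in the text suggests one. The primary outcome, randomization and primary analysis are not affected.

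**What to change.** 1. Restate Aim 2 as the sustained effect of the full package (in-program scheme plus post-program texts and lottery) against standard Go4Fun at 6 and 12 months, in line with Study design.
2. State that Aim 1 at 6 and 12 months is this same package contrast, that only the 10-week contrast isolates the in-program scheme, and that component effects are not estimated.
3. Remove the 10-week item from Aim 2(ii).
4. Reconcile the sentence confining incentives to the 10 weeks with the post-program lottery described in the same section.

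The cost is a narrower claim: the trial will not say whether the texts and lottery work by themselves. Nothing in conduct, the primary outcome or the primary analysis changes. Trial status reports that no data cleaning or analysis had begun at submission; if that still holds, the rewording can precede any results.

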## Methods/Design

### Study design

The study is a cluster RCT (Fig. 1) delivered within the context of the existing Go4Fun program with 10 week, 6 month, and 12 month follow-up (*n* = 40 sites, 570 participants), which compares the effectiveness of participation in the standard Go4Fun program with an enhanced goal setting and structured incentive scheme (intervention) versus participation in the existing Go4Fun program (control). Individual randomization is not possible given the nature of the intervention, so randomization by site will be conducted. Building on our existing research platform, we propose a pragmatic and feasible trial to determine the effectiveness, acceptability, and sustainability of the enhanced intervention at 6 and 12 months after the program. The CONSORT statements for cluster RCTs [43] and for nonpharmacological interventions [44] will be followed.

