### Process evaluation

Process evaluations explore the implementation, receipt, and setting of an intervention and help in the interpretation of outcome results [51]. Information generated from the process evaluation will inform downstream translation by informing policymakers and program developers about the intervention strengths, weaknesses, and areas for improvement. We will use a mixed methods approach to investigate why the incentive scheme may or may not have been effective/sustainable and which intervention components were most influential. Four data sources will be used: (i) quantitative data related to “reach” on participant attendance and outcomes described above; (ii) for those in intervention group, participant and parent/guardian surveys to examine intervention value, satisfaction, utility and health behaviors influenced; (ii) semi-structured interviews with Go4Fun program leaders to investigate implementation along with associated barriers and enablers; and (iv) focus groups with participants and parents/guardians to explore uptake, acceptability and suggestions for improvement. Taken together, qualitative data will explore participant and program leader views on benefits, disadvantages, acceptability of and potential improvements for the incentive scheme. To obtain a broad range of views, we will use a maximum variation sampling method based on patient demographics and health service characteristics [52]. Sampling will continue until no new themes or categories emerge (“thematic saturation”). Analyses will be thematic, and coding will be carried out inductively based on emergent themes. NVivo 9 will be used to assist with interview data management. 

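### Aims 1 and 2 claim separate component effects at 6 and 12 months, but the two-arm design estimates only the effect of the whole package

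*Protocol article*

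**What the plan says.** The aims stand at the end of *Behavioral insights literature* in the Background of the Protocol article. Aim 1 is worded "To determine the effectiveness of a structured goal setting incentive scheme on the following". It covers health outcomes at 10 weeks, 6 months and 12 months, completion of at least 75 % of the program, and goal achievement during the program. Aim 2 is worded "To determine the effectiveness of post program text message reminders highlighting a lottery prize draw". It covers the same health outcomes at 6 and 12 months, and goal achievement at 10 weeks, 6 months and 12 months.

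The allocation is in *Randomization*: "Eligible sites have been randomized to either deliver the intervention (standard Go4Fun plus incentives) or control (standard Go4Fun) program for 10 weeks". *Study design* likewise gives two groups, the enhanced program and the existing one.

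*Intervention group* describes what the one intervention arm receives. During the program, "participants will set SMART [32] behavioral goals and achieving these goals will result in the incentives being provided". After the 10-week program, parents or guardians "will receive weekly mobile phone text message reminders to support and encourage children to achieve their goals", with tickets for a prize draw held at 6 months. *Statistical analysis* plans one kind of outcome comparison, intervention against control.

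**The concern.** Two interventions are each given their own effectiveness aim, for the same outcomes at the same two visits. The same children receive both, and the controls receive neither. The plan describes no third arm, no factorial structure and no second allocation at week 10.

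At stake is how a 12-month difference is attributed. Read through the aims as they stand, one difference could be cited as evidence for the in-program scheme and also as evidence for the texts and lottery. The article presents the latter as a cost-effective way of staying in touch with families, and it directs its results to policymakers. A decision to keep one component and drop the other would have no randomized support.

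**Working it through.** The plan gives no figure for the effect of either component at 6 or 12 months, so there is none to reproduce. The check is which effects the design can identify.

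**Inputs.** Two arms and one allocation (*Study design*, *Randomization*). Content of each arm (*Control group*, *Intervention group*). Texts begin after the 10-week program (*Intervention group*). Planning difference in BMI z score of 0.24 (*Sample size*), used here only as an illustration.

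**Step 1: what differs between the arms at each visit.**

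| Visit | In-program scheme | Texts and lottery |
|---|---|---|
| 10 weeks | differs | not yet started |
| 6 months | differs (already delivered) | differs |
| 12 months | differs (already delivered) | differs |

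**Step 2: one equation per visit.** Let D(t) be the difference between arms at visit t, S(t) the effect of the in-program scheme, and T(t) the further effect of adding texts and lottery to it. Then:

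- D(10 wk) = S(10 wk)
- D(6 mo) = S(6 mo) + T(6 mo)
- D(12 mo) = S(12 mo) + T(12 mo)

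Because T is defined as the increment on top of the scheme, the sums hold by definition. The effect of texts in families who had not had the scheme would be a further unknown. At each later visit there is one equation and two unknowns.

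**Step 3: size of the ambiguity.** Take D(12 mo) = 0.24. The data fit equally well with 0.24 + 0, with 0.12 + 0.12, and with 0 + 0.24. The part due to texts and lottery is therefore anywhere from 0 to 100 % if neither component acts in the wrong direction. Without that condition not even this range holds, since 0.30 − 0.06 = 0.24 fits too. A larger sample makes D more precise but leaves the split open.

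**Step 4: subtracting the 10-week difference.**

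D(12 mo) − D(10 wk) = T(12 mo) + [S(12 mo) − S(10 wk)]

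Suppose both differences are 0.24, so the subtraction gives 0. That fits a scheme whose effect lasts in full (S stays at 0.24) with texts that do nothing (T = 0). It fits equally well a scheme whose effect has gone (S = 0) with texts that contribute 0.24. The bracket cannot be set to zero: *Behavioral insights literature* itself says there is very little research on whether behavior change lasts once incentives stop.

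**Step 5: the 10-week item in aim 2.** Aim 2(ii) lists goal achievement at 10 weeks. The texts start after the program, so this item cannot reflect them.

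**Step 6: what the design does answer.** The 10-week health outcomes, program completion and in-program goal achievement (aim 1(i) at its first visit, 1(ii) and 1(iii)) contrast the in-program scheme with standard Go4Fun, with no texts involved. The 6- and 12-month outcomes contrast the complete package with standard Go4Fun.

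**The case against.** The best defence is that this is a pragmatic trial of a package and partly says so. The abstract describes goals supported by text messages together with rewards. *Study design* speaks of the sustainability of the enhanced intervention at 6 and 12 months. The paragraph that introduces the aims asks whether gains made during the program are maintained. This stands as an account of the trial, and it shows that the package reading is the one the design supports. It does not rescue aim 2, which names the texts and lottery, not the package, as the thing whose effectiveness is determined. Nor can a separate analysis plan help, since no analysis creates the missing comparison. Fig. 1 cannot be seen in the text reviewed, but the text on arms and allocation is explicit.

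Several stronger readings are tempting but not supported:

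- A reader might infer that the primary outcome is compromised. It is not. *Outcomes* and *Statistical analysis* define it as intervention versus control at 12 months and assign it to no single component.
- A reader might infer that the question of "which intervention components were most influential" in *Process evaluation* can yield only participants' opinions. That section also uses attendance and outcome data and interviews with program leaders, and it claims no randomized comparison. All that is needed is to label such findings as non-randomized.
- A reader might take the bracketed label for the intervention in *Randomization* as a misdescription. It is shorthand that *Study design* and *Intervention group* spell out.
- A reader might suppose that control children set no goals. *Control group* includes goal setting in the standard sessions, so the contrast is enhanced against standard goal setting, plus the rewards and later the texts and lottery.
- A reader might conclude that the plan will report one difference twice. *Statistical analysis* has no reporting rule by aim, so this is a risk created by the wording and not a planned step.

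**Conclusion.** The point holds for the wording of the aims. At 6 and 12 months neither the in-program scheme (aim 1) nor the texts with lottery (aim 2) has a separate estimate; only their combined effect does. Aim 2 has no visit at which it can be answered as worded, and its 10-week item precedes the component it is meant to assess. Of the three visits for health outcomes in aim 1, only the 10-week visit isolates the in-program scheme.

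This rests on two readings of the text: that there is a single allocation with no later one, and that the 10-week assessment comes before the first text. The validity of the 12-month primary test, its error rate and the data to be collected are unaffected. The matter is one of attribution, and it should be corrected before results are written up against these aims.

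**What to change.** Reword the aims in *Behavioral insights literature*:

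- **Aim 1:** effect of the in-program goal-setting and incentive scheme on 10-week health outcomes, program completion and in-program goal achievement.
- **Aim 2:** effect of the complete package (in-program scheme, then texts and lottery) versus standard Go4Fun at 6 and 12 months. Remove the 10-week time point from aim 2(ii).
- **Add a statement** that no separate effectiveness claim will be made at 6 and 12 months for the texts, the lottery or the in-program incentives, and that any component findings from the process evaluation are non-randomized.

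This needs no new sites, children, data or analyses, so it can be done although sites are randomized and recruitment has begun. The price is a narrower claim: the trial gives up a stand-alone conclusion about the texts and lottery. To obtain one, the post-program component would have to be randomized separately, which is a different design.
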